#### Sample Size Calculations

Current statistics indicate MV coverage of approximately 75% at 12 months of age in the rural areas of Guinea-Bissau. Drawing on experiences from other studies implementing SMS reminders [13], we aim for an increase in MV coverage of 10 percentage points. Using a significance level of 5% and 80% power, and a hypothesized increased MV coverage to at least 85% in each of the intervention arms (compared to the control arm), a total of 810 children are needed (270 in each arm). Adjusting for expected loss-to-follow-up between 15-20% (eg, outmigration, death, children being vaccinated elsewhere), which is comparable to other mHealth studies [27], we plan to enroll 990 study participants (330 in each arm).

The current median age of MVs given before 12 months of age in rural Guinea-Bissau is approximately 295 days of age [7]. The age distribution is fairly normal, and in the following power calculation we have used a normal approximation: with 270 children in each arm and an MV coverage of at least 75%, we are able to detect a change of 7 days in median age (using a significance level of 5% and 80% power).

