## Methods

### Trial Design

This study is designed as a multi-site, three arm, parallel randomized controlled trial (RCT). Participants will be randomized to either one of two intervention arms (one receiving an SMS reminder, the other receiving the SMS reminder and an additional voice call) or a control arm (no intervention) with a 1:1:1 allocation ratio (Figure 1).

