#### Statistical Analysis

The main outcome of MV coverage at 12 months of age (366 days of age) will be calculated as percent who received MV at the health centers, among all children enrolled. Furthermore, coverage will also be calculated based on follow-up interviews when children reach 13 months of age, among study participants whose children did not receive the MV at the health centers. The coverage (percentages) will be compared using Mantel-Haenszel statistics stratified for health center for each of the intervention groups (SMS and voice calls) compared with the control group. The secondary outcome B (Textbox 1) of timeliness of MVs will compare age distributions between vaccinated children, among all children having received MVs before 12 months of age (366 days), using linear regression adjusted for health center. A statistical significance level of 5% will be used. A subanalysis will stratify for study participants having their own private mobile phone versus those using the phone number of another community member. Due to the groups being randomized, we do not expect baseline imbalances. In the case that such trends do occur, we will be unable to rule out other imbalances or unmeasured confounders. The main outcome will therefore be the crude estimate. However, we will investigate the impact of adjusting for unbalanced background factors in sensitivity analyses. The study will be conducted and reported in accordance with Consolidated Standards of Reporting Trials guidelines [28].

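### The sample size treats the expected 15-20% loss as leaving the analysis, but the main outcome keeps every enrolled child, so the 80% power does not belong to that outcome

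*Protocol article*

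**What the plan says.** The Sample Size Calculations section of the protocol article starts from a control rate: "Current statistics indicate MV coverage of approximately 75% at 12 months of age in the rural areas of Guinea-Bissau". It assumes "a hypothesized increased MV coverage to at least 85% in each of the intervention arms (compared to the control arm"). With "Using a significance level of 5% and 80% power", it concludes that "a total of 810 children are needed (270 in each arm"). It then allows for loss: "Adjusting for expected loss-to-follow-up between 15-20% (eg, outmigration, death, children being vaccinated elsewhere"). On that basis, "we plan to enroll 990 study participants (330 in each arm").

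The Statistical Analysis section calculates the main outcome at 12 months as "percent who received MV at the health centers, among all children enrolled". It adds a further coverage calculation from interviews at 13 months, held for children not vaccinated at the centers. The Follow-Up section says that these interviews are by phone and record MV at another location, a move out of the area, or death. The outcome box lists the primary outcome simply as MV coverage at 12 months, with no limit on where the vaccine was given.

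**The concern.** Inflating 270 to 330 makes sense only if the lost children are removed, leaving about 270 per arm with the full 10-point contrast. The main outcome does not remove them. A child vaccinated elsewhere is outside the numerator by definition. A child who dies or moves away before MV at the center cannot enter it either. All of them remain in the denominator. Neither the 75% nor the 85% is lowered to reflect this.

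The sample size therefore describes one analysis and the statistical section another. At stake is the chance of detecting a reminder effect that is as large as hoped, and the size of the difference that readers will see. The validity of the test is not in question.

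**Working it through.** **Inputs.** From Sample Size Calculations: p1 = 0.75, p2 = 0.85, significance level 5%, power 80%, 270 per arm before and 330 after the loss adjustment, loss L of 15-20%. From Trial Design: "a control arm (no intervention) with a 1:1:1 allocation ratio". Sidedness is not stated. Two-sided is assumed because it reproduces the protocol's figure (one-sided gives 197, or 217 with continuity correction).

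**Step 1: reproduce 270.** With p̄ = (p1 + p2)/2 = 0.80,

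n = [1.96·√(2p̄(1−p̄)) + 0.8416·√(p1(1−p1) + p2(1−p2))]² / (p2−p1)² = 249.98, so 250 per arm.

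Continuity-corrected: n′ = (n/4)·[1 + √(1 + 4/(n·|p2−p1|))]² = 269.6, so 270 per arm. This matches.

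**Step 2: reproduce 330.** 270/(1−0.18) = 329.3, so 330. (15% loss would give 318, and 20% would give 338.) The inflation is the usual one for children who leave the analysis.

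**Step 3: power for the main outcome as defined.** All 330 per arm are analysed. Assume that a fraction L is lost before MV at the center, equally in each arm, and that 75%/85% hold among the rest. The rates become p1(1−L) and p2(1−L).

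Power = Φ{[(p2−p1) − 1.96·√(2p̄(1−p̄)/n)] / √[(p1(1−p1) + p2(1−p2))/n]}, with n = 330. The corrected version subtracts 1/n from the difference.

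Worked case, L = 20%: 60% versus 68%, p̄ = 0.64, 1.96·√(2·0.64·0.36/330) = 0.0732, denominator 0.0372.
- Uncorrected: (0.0800 − 0.0732)/0.0372 = 0.18, power 57.2%.
- Corrected: (0.0800 − 0.0030 − 0.0732)/0.0372 = 0.10, power 54.0%.

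| Effective loss L | Rates | Difference (points) | Power, corrected | Power, uncorrected |
|---|---|---|---|---|
| 5% | 71.25% vs 80.75% | 9.5 | 79.1% | 81.7% |
| 10% | 67.5% vs 76.5% | 9.0 | 70.2% | 73.2% |
| 15% | 63.75% vs 72.25% | 8.5 | 61.7% | 64.9% |
| 20% | 60% vs 68% | 8.0 | 54.0% | 57.2% |

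**Step 4: size needed for 80% power under the same assumptions.** 495 per arm at 15% loss and 589 at 20% (corrected), or 472 and 564 (uncorrected).

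**The case against.** **The timing of the loss is not given.** A reader might infer that the lost children can never be successes. The protocol does not support that. Vaccination is due from 9 months and follow-up runs past 12, so a child vaccinated at the center at 9 months who later moves or dies is already registered as vaccinated. Only loss before MV lowers the numerator, and the protocol does not say how much of the 15-20% that is. This stands, and it is why the low figures are the case in which all loss comes early.

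**The population behind 75% is not given.** If 75%/85% already meant health-center MV among all enrolled, power at 330 would be about 88-90%. The documents argue against this: no loss allowance would then be needed, and the 75% is presented as general rural coverage. If instead the full 10-point difference somehow survived among all enrolled on the lower base, uncorrected power would be about 77-79%. Nothing in the protocol suggests that it would.

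**The 13-month interview.** It can recover children vaccinated elsewhere, one of the three named causes. But the protocol presents it as an additional calculation, not as the main outcome, and it cannot recover deaths or families who are not reached. It mitigates the problem without removing it.

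**Keeping all enrolled children is the sound choice.** Agreed. Analysing everyone randomized protects the comparison, and the error rate under no effect is unaffected. The point is only that the sample size must then use the diluted rates.

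**Conclusion.** The inconsistency between the two sections is certain. The stated 80% power was derived for an analysis that removes the lost children, and the main outcome does not remove them.

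The size is conditional. Corrected power is about 54-62% if three things hold: the full 15-20% is lost before MV at the center, loss is equal across arms and unrelated to the chance of vaccination, and 75%/85% apply to children not lost. An intervention working exactly as hypothesized would then be missed about 38-46% of the time, and the expected difference would be 8.0-8.5 points. With 10% effective loss power is about 70%, and with 5% the planned 80% is nearly kept.

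A reader might infer that true power simply is 54-65%. The documents do not support that: they do not date the loss or define the population behind the 75%, and that range would join a corrected lower end to an uncorrected upper end. Nor does this show an arithmetic slip, since 270 and 330 both reproduce.

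**What to change.** 1. Keep all randomized children as the main denominator. Restate the power for that analysis as a range over the expected loss, with the assumptions on timing, equality across arms and the population behind 75%/85% written out.
2. Count MV by 12 months at any location as success in the main outcome, taking location and date from the planned 13-month interview. This agrees with the primary outcome in the outcome box and recovers children vaccinated elsewhere.
3. Report the health-center-only figure, and any analysis that excludes deaths and moves, as sensitivity analyses.

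Do not make children alive and resident at 9 months the main denominator. Their status would be learned only from phone interviews with families not registered as vaccinated, so exclusions would fall only on non-successes. They would also depend on who can be reached, which may differ by arm because one arm receives voice calls.

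**Cost.** Revised wording, a less favourable stated power, and a date of vaccination added to the interview if it is not already asked. No additional participants are required. Item 2 relies on interview report for MV given elsewhere, and reachability could affect that too, so the health-center-only result should be shown beside it.

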#### Statistical Analysis

The main outcome of MV coverage at 12 months of age (366 days of age) will be calculated as percent who received MV at the health centers, among all children enrolled. Furthermore, coverage will also be calculated based on follow-up interviews when children reach 13 months of age, among study participants whose children did not receive the MV at the health centers. The coverage (percentages) will be compared using Mantel-Haenszel statistics stratified for health center for each of the intervention groups (SMS and voice calls) compared with the control group. The secondary outcome B (Textbox 1) of timeliness of MVs will compare age distributions between vaccinated children, among all children having received MVs before 12 months of age (366 days), using linear regression adjusted for health center. A statistical significance level of 5% will be used. A subanalysis will stratify for study participants having their own private mobile phone versus those using the phone number of another community member. Due to the groups being randomized, we do not expect baseline imbalances. In the case that such trends do occur, we will be unable to rule out other imbalances or unmeasured confounders. The main outcome will therefore be the crude estimate. However, we will investigate the impact of adjusting for unbalanced background factors in sensitivity analyses. The study will be conducted and reported in accordance with Consolidated Standards of Reporting Trials guidelines [28].

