### Follow-Up

When MVs are given in one of the selected health centers, the participants will be registered in the system as having received the vaccination at the given date. The study assistant will also take note of a set of follow-up questions concerning the participants’ motivation for receiving the vaccination as well as a final question as to whether the participant received and understood the text reminder/voice call. The answers to these questions will eliminate the blinding of within the study, since the participants’ answers will reveal their allocation group. In addition, data regarding price of phone call and time spent per phone call will be collected after each call, and analyzed in terms of cost effectiveness.

A qualitative analysis will be done when children reach 13 months of age, for all participants not registered as having received MVs. The analysis will be based on phone interviews to determine the main reasons for not receiving the vaccine, and it will be registered whether the child has received MV at a different location, moved out of the area, or died. All of these participants will be offered MVs for their children.

A selection of participants from each intervention group (n=10-15), who registered their children as having received the MV, will be visited by a study assistant in order to conduct a face-to-face follow-up interview. These interview will focus on the participants’ perception of the intervention message and the overall experience of the intervention. Data collection will rely on digital questionnaires filled out by project assistants during house visits. Difficulty with logistics (ie, locating and visiting the participants) explain the relatively small number of participants selected for this analysis.

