### Development of Reminder Content and Timing

In order to assess the intervention context, and determine the optimal timing and content of the messages to be used in the RCT, a qualitative analysis will be conducted. The analysis will be based on field visits in the rural areas to observe the context for the intervention, including the daily routines for mothers with children aged 6-12 months and their usage of mobile technology. In addition to these observations, a number of semistructured qualitative interviews will be conducted to acquire knowledge about what time of day a message would be preferred, and potential cultural barriers preventing the delivery of messages to household members or neighbors (if the mother does not own a phone).

During the interview, the interviewee will be presented with one of three different versions of the intervention message, and asked questions to evaluate their understanding:

1. A very brief description of measles infection and the reasons for vaccination, inspired by a post card MV reminder intervention that was implementing using the *health belief model* [21].

2. A shorter and more imperative message telling the participant to go to the health center to receive the MV.

3. A verbal message read to the interviewee by the interviewer. The messages will be personalized with the baby’s name and the name of the relevant health center.

All of the messages will be presented in two formats, depending on whether the message is to be delivered directly to the participant’s phone or via the phone of a household member/neighbor. The indirect message variants will be evaluated by presenting them to nearby household members and assessing their understanding and willingness to relay the message.

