**Primary outcome A:**
*MV coverage at 12 months of age.* Difference in MV coverage at 12 months of age between the intervention groups and the control group.

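### The primary outcome counts only doses given at the study health centers, but the reminder can change where a child is vaccinated, so the arm difference can be biased in either direction.

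*Protocol article*

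**What the plan says.** Textbox 1 of the protocol article defines primary outcome A as "Difference in MV coverage at 12 months of age between the intervention groups and the control group". It does not limit where the dose is given.

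The Statistical Analysis section narrows this: "MV coverage at 12 months of age (366 days of age) will be calculated as percent who received MV at the health centers", with all enrolled children as the denominator. The Follow-Up section describes the matching data source: "When MVs are given in one of the selected health centers, the participants will be registered in the system as having received the vaccination".

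Doses at other places are expected. Under Sample Size Calculations, "children being vaccinated elsewhere" is one of the examples of the 15-20% loss to follow-up. For children not registered as vaccinated, the Follow-Up section plans a phone interview at 13 months, at which "it will be registered whether the child has received MV at a different location, moved out of the area, or died". The Statistical Analysis section then adds a second calculation: "coverage will also be calculated based on follow-up interviews when children reach 13 months of age, among study participants whose children did not receive the" vaccine at the health centers.

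The intervention acts on place and day. The Intervention section describes it as matching children to vaccination days, either at the local health center or on an outreach day. Under Development of Reminder Content and Timing, the messages carry "the name of the relevant health center".

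**The concern.** Three sections treat the same child differently. For a child vaccinated by 366 days at a place other than a study center, Textbox 1 gives a success, the Statistical Analysis section gives a failure that stays in the denominator, and the sample size section gives a loss to follow-up.

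If reminders had no influence on place, counting only center doses would lower the counted coverage in every arm and mainly cost power. Here the reminder names a place and a day, so the misclassification can depend on the arm, and randomization does not remove that. A mother who would have used another site may come to the center because of the message. Her child then counts as vaccinated, while the same child in the control arm would count as unvaccinated. Conversely, a mother directed to an outreach day drops out of the numerator if outreach doses do not count as center doses.

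The article says that policy-makers need solid evidence on which to base decisions. A difference in center-only coverage could be reported to them as a difference in coverage when part or all of it is a change of venue.

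**Working it through.** **Inputs from the protocol article (Sample Size Calculations):** control coverage 75%, target 85%, significance level 5%, power 80%, 270 children per arm before loss, 330 per arm enrolled, loss 15-20%. Sidedness is not stated; two-sided is assumed.

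**The plan's own figure.** The two-sided two-proportion formula gives n = [1.96 × √(2 × 0.80 × 0.20) + 0.842 × √(0.75 × 0.25 + 0.85 × 0.15)]² / 0.10² = 250 per arm. The continuity correction, (n/4) × [1 + √(1 + 4/(n × 0.10))]², raises this to 270. That matches the stated figure. Allowing for 18% loss, 270/0.82 = 330, which lies within the stated loss range. These figures are not in dispute.

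**Assumptions that are not in the documents.** True any-site coverage is 75% in every arm, so there is no real effect. A share e of all children in the control arm is vaccinated elsewhere. The reminder moves a fraction s of those children to the study center.

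- Counted coverage, control arm: 0.75 − e
- Counted coverage, reminder arm: 0.75 − e(1 − s)
- Spurious difference: e × s
- True any-site difference: 0

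**Worked case, e = 10%, s = 50%, 330 per arm.** Counted coverage is 65% against 70%. The pooled standard error is √(2 × 0.675 × 0.325/330) = 0.0365, so the test rejects beyond 1.96 × 0.0365 = 0.0715. The unpooled standard error is 0.0364. The chance of rejection in favor of the reminder is Φ((0.05 − 0.0715)/0.0364) = Φ(−0.59) = 28%. Rejection in the other direction adds less than 0.1%.

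| e (elsewhere) | s (moved) | Counted, control vs reminder | Spurious difference | Rejection rate (nominal 5%) |
|---|---|---|---|---|
| 5% | 25% | 70.0% vs 71.25% | 1.25 points | 6% |
| 10% | 25% | 65.0% vs 67.5% | 2.5 points | 10% |
| 15% | 25% | 60.0% vs 63.75% | 3.75 points | 17% |
| 5% | 50% | 70.0% vs 72.5% | 2.5 points | 11% |
| 10% | 50% | 65.0% vs 70.0% | 5 points | 28% |
| 15% | 50% | 60.0% vs 67.5% | 7.5 points | 52% |

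Rates are two-sided, per comparison with control, from the normal approximation, and ignore stratification by center.

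**Opposite direction.** If reminders move doses from the center to outreach days and outreach doses are not counted, the difference changes sign. Exchanging the two counted percentages in any row gives the same rejection rate, now against the reminder.

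**Any-site numerator.** The difference is 0 under every combination of e and s, and the test keeps its nominal 5%.

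**The case against.** The strongest reply is that the protocol already plans the data needed to detect a change of venue. The sentence after the main outcome definition adds coverage from the 13-month interviews, and the next one compares the coverage percentages by arm. Center doses plus interview doses would give any-site coverage. This stands in part: the information is to be collected, and a combined analysis may be intended. But the text presents the interview calculation as an addition and describes it among children without a center dose. That group is formed after randomization, so coverage within it cannot correct the primary comparison. Nothing says that the two are merged, or which leads.

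The size is also open to challenge. The documents give neither e nor s. The 15-20% loss also covers outmigration and death, so e = 15% uses most or all of that allowance and means that one vaccinated child in five (15/75) goes elsewhere. Mothers must live in the center's uptake area, and distance to neighboring centers is a selection criterion. Children vaccinated after moving away would not readily be redirected by a message. All of this stands, and it makes the lower rows of each block less likely. It does not bring e to zero, because the plan itself lists vaccination elsewhere.

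Finally, center registration is prospective and dated, whereas the interview relies on reaching mothers by phone and on their report. That is a fair reason to keep the center-only measure, but not to call it coverage without a site limit.

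A reader might go further and infer that the error favors the intervention, or that the trial will report a gain that is only a change of venue. The documents do not support either: outreach reminders can push the other way, and the planned interviews could expose a shift. Nor do they show that a child already vaccinated in another activity would be vaccinated again and counted at the center; the ethics section plans follow-up, as far as possible, to avoid reminding such families.

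**Conclusion.** The point holds as a flaw in how the primary outcome is fixed. As written, it measures vaccination at a study center, while Textbox 1 names vaccination coverage, and the intervention can act on the difference between the two. The bias is possible, not certain, and its direction is not established.

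Its size runs from negligible (6% rejection against 5%, with 5% elsewhere and a quarter moved) to large (52%, with 15% elsewhere and half moved). The whole range rests on assumed values of e and s, on 75% any-site coverage in every arm and on 330 children per arm. It shows what the definition allows, and does not forecast what will happen. The contradiction between the sections does not depend on these assumptions.

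**What to change.** - **Primary outcome.** In Textbox 1 and the Statistical Analysis section, define it as any measles vaccination by 366 days of age, wherever given (center, outreach or elsewhere), among all children enrolled in each arm. Combine center registration with the 13-month interview.
- **Date of dose.** Ask for it at that interview, read out by the mother from the vaccination card where possible. Otherwise doses given between 366 days and 13 months could be counted.
- **Center-only coverage.** Keep it as a secondary or sensitivity outcome under a name that says what it is.
- **Reporting.** Give the number of doses elsewhere by arm, and show a bound in which children of mothers not reached count as unvaccinated.
- **Sample size section.** Reconcile it with the analysis, so that a child vaccinated elsewhere is not a loss in one and a failure in the other.

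The cost is a change of wording and one added question at a contact that is already planned. The downside is that part of the primary then depends on phone reach and maternal report, since a card cannot be inspected by phone. The bound shows the effect of mothers not reached, and the center-only analysis shows how far the result depends on reported doses.

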### Intervention

The intervention being evaluated is a cell phone reminder and coordination system, which seeks to coordinate potential recipients of MV with MV opportunities (ie, days in which MV is administered either at their local health center, or at a relevant outreach day). Participants allocated to intervention groups will receive two SMS text reminders in the local language of Portuguese Creole. The first message will be delivered three days before the suitable MV opportunity, and the second will be sent one day before. If the participant is allocated to also receive a phone call, a project worker will call the supplied phone number two days before the MV opportunity.

SMS messages are *active* in the cell phone network for 24 hours, after which the delivery attempt will be considered failed. If the delivery attempt of a first message fails (ie, three days before MV opportunity), the message will be redelivered. If delivery of the second message fails (ie, one day before MV opportunity), it will not be redelivered due to time rendering it irrelevant. If a phone call fails it will be reattempted two times: once on the same day, and a final attempt on the day before MV opportunity. We will register all failed message delivery attempts and account for these in the subsequent analysis.

If several phone numbers are supplied, SMS texts will be sent to all phone numbers. Voice calls will made to one number, and if the call to the first number is not successful, the second number will be attempted, and so on. Voice calls, like the SMS texts, will be made in the Creole language.

If a study participant does not arrive at the MV opportunity, or if the MV opportunity is cancelled or unavailable for any reason, the study participant will receive a new set of messages/voice calls at the next relevant MV opportunity, assuming the child is still eligible (ie, child is 9-12 months of age). The new set of messages will be delivered regardless of whether earlier delivery attempts for the participant failed.

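### The main outcome counts only measles vaccine given at the health centers, so it mixes whether a child was vaccinated with where, and it disagrees with the stated outcome and the sample size

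*Protocol article*

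**What the plan says.** - **Outcome as named.** Textbox 1, primary outcome A: "Difference in MV coverage at 12 months of age between the intervention groups and the control group". Nothing limits where the dose is given.
- **Outcome as calculated.** Statistical Analysis: the main outcome "will be calculated as percent who received MV at the health centers, among all children enrolled".
- **Second figure.** The same section adds that "coverage will also be calculated based on follow-up interviews when children reach 13 months of age". Its wording ties this figure to families with no center dose, and it is not called the main outcome.
- **Where reminders point.** The Intervention section defines the vaccination opportunities as "days in which MV is administered either at their local health center, or at a relevant outreach day".
- **How doses are recorded.** Follow-Up: "When MVs are given in one of the selected health centers, the participants will be registered in the system as having received the vaccination". For participants not so registered, a phone interview at 13 months is planned, in which "it will be registered whether the child has received MV at a different location, moved out of the area, or died".
- **Sample size.** Sample Size Calculations uses 75% versus 85% coverage and 270 children per arm. It raises this to 330 per arm for a 15–20% loss to follow-up, and vaccination elsewhere is one of the listed reasons for loss.

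**The concern.** The same child is handled in three ways. For a child vaccinated at another facility before 12 months, primary outcome A implies a success, the sample size section implies a loss, and the Statistical Analysis section implies a failure that stays in the denominator. The 75% and 85% used for sizing are described as coverage, so the contrast that was sized is not the one that will be tested.

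This matters most if the share vaccinated off-center differs by arm. The intervention tells mothers when and where to come, and controls get no such message. Reminders could draw to the center some children who would have been vaccinated elsewhere, and the main outcome would then show a gain although no extra child was protected. Even if the off-center share is the same in all arms, scoring those children as failures shrinks the observed difference and costs power.

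**Working it through.** **Inputs from the document:** 75% and 85% coverage, 5% significance level, 80% power, 270 needed and 330 enrolled per arm (Sample Size Calculations). **Not in the document:** the share vaccinated elsewhere, and the part of that share that reminders would move. Both are assumed below.

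**1. Reproducing the plan's figure.** Two-sided test with mean rate 0.80:

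n = [1.96·√(2·0.80·0.20) + 0.842·√(0.75·0.25 + 0.85·0.15)]² / 0.10² = 250.

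With continuity correction: (250/4)·[1 + √(1 + 4/(250·0.10))]² = 270. This matches the plan. Enrolling 330 implies a loss of 1 − 270/330 = 18.2%, inside the stated range. The sample size arithmetic is sound for coverage.

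**2. Power formula for the scenarios** (pooled null variance, no continuity correction):

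Power = Φ[(d − 1.96·SE₀)/SE₁], where d is the difference, SE₀ = √(2·p̄(1−p̄)/n) and SE₁ = √(p₁(1−p₁)/n + p₂(1−p₂)/n). This is the chance of a significant result in the direction of d.

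For 75% versus 85% with n = 330, SE₀ = 0.0311, SE₁ = 0.0309 and power is 0.90. With n = 270 it is 0.83.

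**3. No true effect, place shifted by reminders.** True coverage is 75% in both arms and e is the share of all control children vaccinated elsewhere. Reminders move half of e to the center. The main outcome then compares 75% − e with 75% − e/2.

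| e (assumed) | Control | Intervention | Spurious gain | Chance of p<0.05 favouring reminders |
|---|---|---|---|---|
| 5% | 70.0% | 72.5% | 2.5 points | 0.105 |
| 10% | 65.0% | 70.0% | 5.0 points | 0.278 |

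For the first row, SE₀ = SE₁ = 0.0352 and (0.025 − 0.0690)/0.0352 = −1.25, so Φ = 0.105. The nominal rate is 2.5% in that direction, or 5% in both. Adding the opposite direction (0.004 in the first row) gives 0.11 and 0.28.

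The result depends on the half. If only a quarter of e = 10% moves, the comparison is 65.0% versus 67.5%: SE₀ = SE₁ = 0.0368, (0.025 − 0.0721)/0.0368 = −1.28, and the chance is 0.10.

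**4. True effect of 75% versus 85%, same off-center share in all arms.** Here s is the share of vaccinated children who are vaccinated off-center, and the observed rates are 75%·(1 − s) and 85%·(1 − s), with n = 330.

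| s (assumed) | Control | Intervention | Power |
|---|---|---|---|
| 0 | 75.0% | 85.0% | 0.90 |
| 5% | 71.3% | 80.8% | 0.82 |
| 10% | 67.5% | 76.5% | 0.73 |

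At 10%, power is below the planned 80% although all 330 children per arm are analysed.

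**The case against.** **The interviews already pick up doses given elsewhere.** This largely stands. The 13-month interview goes only to participants not registered as vaccinated, so the restriction in "among study participants whose children did not receive the MV at the health centers" probably describes who is interviewed, and the reported doses would be added to the center doses. A reader might infer that the plan compares arms within a subset formed after randomization. The wording allows that reading but does not establish it. What remains is that this figure is not the main outcome, its denominator is ambiguous, and the 366-day limit is not restated for it.

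**Outreach doses may count as center doses.** This stands. A reader might infer that a mother who follows a reminder to an outreach day is scored as a failure. The Intervention section lists outreach separately from the center and Follow-Up describes registration at the centers, but nothing says how outreach doses are recorded. The document leaves this unclear; it does not state an exclusion.

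**The design limits vaccination elsewhere.** Mothers must live in the center's uptake area, and centers are chosen partly on distance to neighbouring centers. The 15–20% loss also has to cover outmigration and death, and a family that has moved away is unlikely to be drawn back. This is why the table in step 3 stops at 10%. Larger shares would use up most of the allowance, and no document supports the half that is assumed to move.

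**The center-only outcome has merits.** It is dated prospectively and is defined for every enrolled child. Interview data bring phone-reported dates and families not reached. That is a fair argument for keeping center-only coverage as a supporting analysis, but it does not resolve the conflict with primary outcome A.

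**Conclusion.** The concern holds. As written, the main outcome scores timely vaccination elsewhere as non-vaccination, which conflicts with primary outcome A and with the sample size section. It would be too strong to say that the outcome measures place instead of coverage: a child never vaccinated scores zero under either definition, so the outcome mixes the two.

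The size cannot be known from the document. Under the assumptions in step 3 (5–10% of control children vaccinated elsewhere, half of that share moved), the spurious gain is 2.5–5 points and the chance of p<0.05 about 11–28%. Under an equal off-center share of 10% of vaccinated children, power falls from 0.90 to 0.73. If the share elsewhere is very small, or reminders do not change place, the bias between arms is small. The definitions would still need to be reconciled.

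**What to change.** - Define the primary outcome as MV at any location (center, outreach or other facility) on or before 366 days of age, over all randomized children. Use one numerator and one denominator, combining center registrations with the 13-month interview.
- Add place of vaccination and the date on the vaccination card to that interview.
- State that outreach doses count.
- Keep center-only coverage as a sensitivity analysis.
- Make Sample Size Calculations and Statistical Analysis agree on children vaccinated elsewhere.
- Report by arm how many families were not reached at 13 months, with a sensitivity analysis that counts their children as unvaccinated.

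The cost is small because the interview is already planned for every participant not registered as vaccinated: revised wording and two added questions. The real downside is in the data. Some dates will be read out over the phone and not seen, and vaccination status will be unknown for families not reached.
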